#### Disease activity

Patients will be assessed for disease activity using the Compound Disease Activity Index (CDAI) [42] which provides a score comprised of tender joint count (TJC), swollen joint count (SJC), patient global assessment (PGA), and physician global assessment (MGA) calculated as follows:CDAI=TJC+SJC+PGA+MGA

This score allows for the classification of patients according to the severity of their disease where a score <2.8 indicates remission, a score <10 indicates moderate disease activity, a score <22 indicates moderate disease activity, and a score >22 indicates severe disease activity. The physician will be blinded as to the grouping of participants during assessments.

#### Inflammation

Patients will be assessed for acute inflammation by measuring C-reactive protein (CRP) concentration from a 10 ml venous sample.

#### Pain

At each assessment, patients will be asked to rate their pain levels over the previous week using a Lickert scale ranging from 0–5, where a score of 0 indicates no pain and a score of 5 indicates unbearable pain. Furthermore, at each WBV session, patients will be asked to rate their pain levels on that day using the same Lickert scale.

#### Fatigue

At each assessment, patients will be asked to rate their fatigue levels over the previous week using a Lickert scale ranging from 0–5, where a score of 0 indicates not feeling tired at all, and a score of 5 indicates the most tired ever felt.

#### Anthropometry

Height and weight will be measured to the nearest cm and kg respectively using a standard stadiometer and scale, with patients barefoot and wearing minimal clothing. Thereafter body mass index (BMI) will be calculated.

#### Body composition

Body composition, including fat mass and lean muscle mass will be taken from the DXA scan. Percentage body fat and percentage lean muscle mass will then be calculated. Appendicular lean mass (ALM) will also be calculated and used to classify those patients with sarcopenia.

### Statistical analysis

Statistical analysis will be carried out using Stata version 12/IC 12.0. All data will be presented as mean ± SD, and a p value ≤0.05 will be considered significant. Data will be analysed on an intention to treat basis. Student’s unpaired t-tests will be used to compare absolute, as well as change in HAQ, BMD, physical activity, patient characteristics, and RA disease activity data between the WBV group and CON group at baseline. Cohen’s D effect sizes will be calculated to determine the magnitude of effects observed.

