### Sample size

A sample size calculation (ß = 0.10) based on detecting a minimum clinically important difference of 0.22 in HAQ score (using an SD of 0.19) [36] between the two groups, showed that at a 5% level we would require a sample of 8 participants in each group with a power of 90%.

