### Potential obstacles

Potential obstacles include adherence to the protocol, and attempting to minimise the attrition rate of the study. Participants will be in regular contact with the primary investigator who will attempt to minimise attrition, as well as follow up on patient’s health on a weekly basis. The short duration of the study, as well as the intermittent design of the study, lead us to expect an attrition rate of approximately 20% according to a meta-analysis by Linke et al. in 2009 [43]. There is the potential that WBV may cause adverse effects or may not be tolerated in some participants; however the primary investigator will observe every WBV session, and assess pain levels at each WBV session in order to monitor this. It is also possible that WBV will have no effect on the outcomes measured.

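### The only between-group analysis named is a pair of unadjusted t-tests (absolute and change), worded as done at baseline; one baseline-adjusted HAQ analysis should replace them

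*Protocol article*

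**What the plan says.** The Statistical analysis section of the protocol article fixes the method: "Student’s unpaired t-tests will be used to compare absolute, as well as change in HAQ, BMD, physical activity, patient characteristics, and RA disease activity data". The sentence ends "between the WBV group and CON group at baseline". The same section states "Data will be analysed on an intention to treat basis" and "a p value ≤0.05 will be considered significant", and adds Cohen's D. It names no baseline-adjusted or repeated-measures model, and does not say whether the absolute value or the change, or month 3 or month 6, is primary.

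Table 1 schedules HAQ at months 0, 3 and 6. Under Study design, patients are allocated alternately on enrolment. Under Participants, 50 are to be recruited. Under Potential obstacles, the duration and design of the study "lead us to expect an attrition rate of approximately 20" per cent, with no visit attached to that figure. The same section allows that some patients may not tolerate the vibration training.

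**The concern.** There are three difficulties.

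1. Read literally, the sentence places every test at baseline, including the test of change. No follow-up comparison is then properly specified. The tests are presumably meant for the follow-up visits, and the working below treats them so.
2. Two tests of the same outcome are planned and neither is named as decisive. They respond in opposite directions to a baseline difference, so the reading of the trial could depend on which is preferred afterwards. With about 25 per group, some chance imbalance in HAQ is to be expected. With alternation in place of randomisation, imbalance need not be chance alone.
3. A t-test of a visit, or of change to it, can use a patient only if that visit's value was observed or imputed. The article expects appreciable attrition, and only the vibration group has 24 sessions to attend. Losses could therefore be unequal and related to outcome.

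**Working it through.** **Inputs.** From Sample size: HAQ difference 0.22, SD 0.19, 5% level, 90% power. From Participants and Potential obstacles: 50 patients and about 20% attrition. Assumptions: equal groups (25 each), two-sided testing, 0.19 is the SD of the HAQ score and is the same at both visits, and baseline to month-3 correlation ρ between 0.3 and 0.9. The article gives no value for ρ.

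**The plan's own figure.** The article says "we would require a sample of 8 participants in each group with a power of 90" per cent. The two-group formula gives n = 2 × (1.960 + 1.282)² × 0.19² / 0.22² = 15.67, so 16 per group, or 17 by the noncentral t. Without the factor 2 the result is 7.84, which rounds to the stated 8. That is a separate matter and does not drive this point, because 50 patients are planned.

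**Precision.** Relative to the variance of the absolute score, the error variance is 1 for the absolute-score test, 2(1 − ρ) for the change-score test and 1 − ρ² for the baseline-adjusted analysis.

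| Assumed ρ | Absolute | Change | Adjusted | Cut against the better t-test |
|---|---|---|---|---|
| 0.3 | 1 | 1.40 | 0.91 | 9% |
| 0.5 | 1 | 1.00 | 0.75 | 25% |
| 0.7 | 1 | 0.60 | 0.51 | 15% |
| 0.8 | 1 | 0.40 | 0.36 | 10% |
| 0.9 | 1 | 0.20 | 0.19 | 5% |

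These factors ignore the one degree of freedom spent on the covariate.

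**Imbalance.** If the groups differ by d at baseline, the absolute-score difference is shifted by ρd and the change-score difference by −(1 − ρ)d. The two estimates therefore disagree by exactly d. By chance alone, with 25 per group, the standard error of d is 0.19 × √(2/25) = 0.054, so its 95% range is about ±0.105. That is 0.105 / 0.22 = 48% of the target difference. At d = 0.105 the shifts are:

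- ρ = 0.5: +0.053 (absolute) and −0.053 (change)
- ρ = 0.7: +0.074 and −0.032
- ρ = 0.8: +0.084 and −0.021

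**Missing visits.** 20% of 50 is 10 patients, leaving about 40, or 20 per group. Without imputation, up to about 10 would be absent from a given follow-up comparison. The number is smaller at month 3 if some losses come later.

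**Power after attrition** (noncentral t, 20 per group, difference 0.22, SD 0.19). The absolute-score test has 94.6%. At ρ = 0.5 the change-score test also has 94.6% and the adjusted analysis 98.5%. At ρ = 0.3 the change-score test has 85.4% and the adjusted analysis 96.2%. The comfort depends on the SD: at an assumed 0.30, the absolute-score test has 61.8% and the adjusted analysis at ρ = 0.5 has 74.2%.

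**The case against.** The strongest reply is that the plan is coherent enough. Intention to treat fixes the group in which a patient is analysed, and a t-test can be run on imputed values. The handling of missing visits may stand in a fuller protocol or analysis plan that is not shown. The change score does use each patient's baseline. With about 40 completers the stated inputs still give roughly 95% power for the absolute-score test, so the loss of precision does not endanger the primary comparison.

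Much of this stands, and it rules out several stronger readings:

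- A reader might infer that the t-tests contradict the intention-to-treat statement. The article never says that patients with a missing visit are dropped, so there is a tension but no contradiction in the text.
- A reader might infer that baseline HAQ goes unused. That is true only of the absolute-score test.
- A reader might infer that drop-out will favour the vibration group. The article gives no attrition by group, so the direction is conjecture.

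The reply does not answer the rest. The choice of test is not left open: the article states it, without baseline adjustment, in two versions with neither given priority, and with a timing that cannot apply to change.

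**Conclusion.** The point holds as an improvement that should be made, not as a flaw that invalidates the trial. The named analysis needs rewriting in any case, because a test of change cannot be done at baseline. One baseline-adjusted analysis would replace two tests that a baseline imbalance pulls apart by its full size, plausibly up to about 0.105 HAQ units by chance alone against a target of 0.22. It would also reduce error variance by 25%, 15% or 10% against the better t-test at ρ of 0.5, 0.7 or 0.8. These sizes rest on the assumed correlations and, for the imbalance, on reading 0.19 as the SD of the score.

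Adjustment has limits. It does not remove selection bias from alternating allocation. A mixed model deals with drop-out only if data are missing at random, which may fail if patients who worsen or cannot tolerate the sessions leave.

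**What to change.** Replace the t-test sentence with one primary analysis: the group difference in month-3 HAQ, adjusted for baseline HAQ, with patients in their allocated group. Two forms would serve:

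- **ANCOVA** of month-3 HAQ on group and baseline HAQ. Without imputation it still omits patients who lack month 3, so the missing-data approach must be stated with it.
- **A mixed model** of HAQ at months 3 and 6, with group, visit, group by visit and baseline HAQ as a covariate. It uses partial follow-up under missing at random. Patients with no follow-up value still add nothing to the contrast.

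Do not constrain the baseline means to be equal, because that relies on randomisation and allocation here alternates. Remove the words that tie the tests to baseline. Use the same model for BMD, CDAI and physical activity, and add one sensitivity analysis for non-random drop-out.

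The cost is one paragraph of wording, a few lines of analysis code and one degree of freedom for the covariate. No new data or patients are needed.

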**Methods/Design:**

This study is a semi randomised, controlled trial consisting of a cohort of patients with established RA assigned to either a WBV group or a CON (control) group. Patients in the WBV group will undergo three months of twice weekly intermittent WBV sessions, while the CON group will receive standard care and continue with normal daily activities. All patients will be assessed at baseline, following the three month intervention, and six months post intervention. Main outcomes will be an improvement in functional ability as assessed by the HAQ. Secondary outcomes are attenuation of loss of bone mineral density (BMD) at the hip and changes in RA disease activity, HRQoL, habitual physical activity levels and body composition.

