### Outcome measures

All outcomes will be measured at baseline, and reassessed after the three month intervention, as well as again three months post intervention. The primary outcome of this study will be an improvement in functional ability as assessed by the HAQ. The secondary outcomes will be attenuation in loss of BMD at the hip, as well as improvements in subjective pain scores, SF-36, CDAI, and objective habitual physical activity levels (Table 1).

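### The only stated hypothesis test is placed at baseline, and neither one HAQ measure nor one visit is named as primary, so the primary outcome has no defined test

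*Protocol article*

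**What the plan says.** The Statistical analysis section of the protocol article says that "unpaired t-tests will be used to compare absolute, as well as change in HAQ, BMD, physical activity, patient characteristics". The end of that same sentence fixes who is compared and when: "RA disease activity data between the WBV group and CON group at baseline". Baseline is the only time point in the section. The threshold is that "a p value ≤0.05 will be considered significant"; whether tests are one- or two-sided is not stated. The only other analysis is Cohen's D: "effect sizes will be calculated to determine the magnitude of effects observed". That is an effect size, not a test.

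Under Outcome measures, "The primary outcome of this study will be an improvement in functional ability as assessed by the HAQ". Neither a visit nor a form of the score (level or change) is attached. The same section says "All outcomes will be measured at baseline, and reassessed after the three month intervention, as well as again three months post intervention", and Table 1 agrees with months 0, 3 and 6. The Abstract differs on the last visit: "All patients will be assessed at baseline, following the three month intervention, and six months post intervention".

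**The concern.** The sentence contradicts itself. A change score needs a later measurement, so it cannot be compared at baseline, and a comparison of the groups at baseline says nothing about the intervention. No other sentence supplies a post-intervention test of HAQ.

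Replacing baseline with follow-up does not settle the matter. Two forms of the score and two follow-up visits leave four candidate tests of the primary outcome, each with its own 5% threshold. Whoever analyses the data would choose among them, possibly after seeing results.

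The two forms can also disagree. A test on absolute scores and a test on change respond in opposite directions to a baseline difference between the groups, and the groups here are small. Baseline HAQ is collected, but neither form adjusts for it.

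**Working it through.** **Is a test singled out anywhere?** The places that could do so, side by side:

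- *Statistical analysis*: absolute and change both listed, unranked; the only time point is baseline.
- *Outcome measures* and *Functional ability*: HAQ is primary; no visit, no form of the score.
- *Table 1*: HAQ at months 0, 3 and 6; none marked as primary.
- *Sample size*: a between-group HAQ difference of 0.22 with SD 0.19; no visit named, and not said whether the SD is of a score or of a change. Its result does not help either: the stated 8 per group comes from the formula without the two-group factor, (0.19 × (1.960 + 1.282) / 0.22)² = 7.84, whereas a two-group comparison needs 2 × 7.84 = 15.67, so 16. That is a separate matter, and the planned 50 participants cover it.
- *Discussion*: the post-intervention assessment serves to examine sustainability. This hints that month 3 is the main visit but does not say so.

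None of them names one HAQ test.

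**False-positive risk.** The plan gives no figure to reproduce here. Inputs: 50 recruited (Participants) and about 20% attrition (Potential obstacles) give 50 × 0.8 / 2 = 20 per group; threshold 0.05. The correlation r between visits is not in the document; it is assumed equal for all pairs of visits and varied from 0.3 to 0.9.

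If tests were independent, the chance of at least one p ≤ 0.05 would be 1 − 0.95² = 9.75% for two and 1 − 0.95⁴ = 18.5% for four. HAQ tests on the same patients are correlated, so 40,000 null trials were simulated for each r:

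| r | Any of four tests | Absolute or change, month 3 | Change, month 3 or 6 |
|---|---|---|---|
| 0.3 | 16.2% | 9.0% | 9.2% |
| 0.5 | 16.0% | 8.8% | 8.9% |
| 0.7 | 16.1% | 9.3% | 9.2% |
| 0.8 | 15.7% | 9.6% | 8.9% |
| 0.9 | 15.2% | 9.5% | 9.1% |

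A separate run at r = 0.5, 0.7 and 0.8 gave 16.4%, 16.0% and 15.8% for any of four, and 9.2%, 9.3% and 9.5% for month 3 alone. The result hardly depends on r. One pre-specified test has 5%.

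**Baseline difference.** With equal variances, an observed baseline difference D shifts the expected absolute-score difference by rD and the expected change-score difference by −(1 − r)D. If 0.19 is taken as the SD of a score (an assumption), the standard error of D is 0.19 × √(2/20) = 0.060, or 0.060 / 0.22 = 27% of the target difference. For a D of that size and r = 0.7, the shifts are +0.042 and −0.018; at r = 0.5 they are +0.030 and −0.030. Analysis of covariance (ANCOVA) removes both.

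**Precision.** Relative to the absolute-score test, the variance is 1 for absolute scores, 2(1 − r) for change and 1 − r² for ANCOVA.

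| r | Absolute | Change | ANCOVA | ANCOVA / absolute | ANCOVA / change |
|---|---|---|---|---|---|
| 0.5 | 1 | 1.00 | 0.75 | 75% | 75% |
| 0.7 | 1 | 0.60 | 0.51 | 51% | 85% |

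**The case against.** Nobody would run a change-score test at baseline; the phrase is plainly misplaced. Because patient characteristics are in the same list, the sentence may have merged two tasks: absolute values compared at baseline, and change compared between groups as the treatment effect. Taken with the sustainability role of the last visit, that would leave change at month 3 as one valid test at 5%. The article contains no rule that any significant result counts as success. An unpaired t-test on change is a legitimate analysis, and on the plan's own inputs 20 per group already gives about 95% power, so the precision gained by adjustment is not critical. Alternating allocation does not in itself increase chance imbalance; its hazard is predictability, which adjustment for HAQ would not fully cure. Finally, the article is condensed, and a SAP may name the primary contrast.

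Much of this stands. The 16% is the top of a range, and ANCOVA is a better choice rather than the correction of an invalid one. What does not stand is the inference that the matter is settled. The merged-task reading has to be reconstructed by the reader, and nothing in the text prefers it to the others. Nor is this detail left to a SAP: the article chose to state the test, both forms of the score, the threshold and the time point, and stated the time point wrongly. A SAP that placed the tests at follow-up would contradict the published text.

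**Conclusion.** The concern holds. As written, the only hypothesis test cannot assess the intervention, and no reading of the text yields one declared test of the primary outcome. The chance of at least one significant HAQ result under no effect runs from 5% (change at month 3 only) through about 9% (two candidate tests) to about 16% (all four). These figures assume 20 per group, normally distributed scores and equal correlation between visits; they vary little for correlations from 0.3 to 0.9. The central defect depends on none of these assumptions, nor on a preference for ANCOVA. Since it concerns the only test of the primary outcome, it needs correcting before outcome data are examined.

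**What to change.** Replace the sentence on t-tests with text to this effect:

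- The single primary analysis is the between-group difference in HAQ at month 3, estimated by ANCOVA with baseline HAQ as covariate, reported with a 95% confidence interval and tested at the two-sided 5% level.
- HAQ at the later visit is a secondary analysis of sustainability. Its timing must be reconciled between the Abstract and the Outcome measures section with Table 1.
- BMD, CDAI and physical activity use the same baseline-adjusted model and are secondary.
- Baseline characteristics are summarised by group without significance tests.

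If the investigators prefer the t-test on change, naming change at month 3 as the sole primary test would also close the gap, with less precision. The cost is rewording and a dated record of the choice. No new data are needed, and the analysis runs in the software already named.

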### Potential obstacles

Potential obstacles include adherence to the protocol, and attempting to minimise the attrition rate of the study. Participants will be in regular contact with the primary investigator who will attempt to minimise attrition, as well as follow up on patient’s health on a weekly basis. The short duration of the study, as well as the intermittent design of the study, lead us to expect an attrition rate of approximately 20% according to a meta-analysis by Linke et al. in 2009 [43]. There is the potential that WBV may cause adverse effects or may not be tolerated in some participants; however the primary investigator will observe every WBV session, and assess pain levels at each WBV session in order to monitor this. It is also possible that WBV will have no effect on the outcomes measured.

## Discussion

The present study will contribute to the current field of rheumatology by potentially providing a non-pharmacological means to improve functional ability and attenuate the loss of BMD associated with RA. This study may provide a safe, sustainable exercise intervention for these patients that could potentially improve certain aspects of disease activity, as well as HRQoL and habitual physical activity.

The advantages of the present study over previous exercise interventions in RA include, firstly, the use of a novel therapy in RA. WBV therapy has not previously been used in patients with RA (to the best of our knowledge), and could provide a safe and easy form of exercise for patients who are often unable to participate in strenuous activities. Furthermore, the application of an intermittent WBV programme could potentially exhibit the added benefit over the previous HRQoL and strength benefits seen following WBV therapy in other rheumatic diseases, of attenuating BMD loss in these patients. Very few studies have focused exercise interventions on improving or attenuating the loss in BMD in this population, despite the very high prevalence of osteoporosis that exists. Usually, interventions designed to increase BMD are dynamic and strenuous, which is not feasible in an RA population. WBV therapy could provide a solution to this problem.

Secondly, the use of an objective measurement of physical activity could further elucidate the benefits of the WBV intervention by providing an accurate, and detailed description of changes that may occur during and following the WBV intervention. Accelerometry allows for the novel examination of changes in patterns of habitual physical activity in this population following the intervention, which will help elucidate which thresholds of physical activity are affected by WBV therapy. Previous research conducted by the authors has shown by using accelerometry for the first time in this population as a means to compare physical activity levels to healthy control participants, that patients with RA are extremely sedentary, and that patients with higher levels of physical activity fare better on certain disease activity and HRQoL outcomes [12]. The potential ability of WBV therapy to increase physical activity levels could therefore attribute to any changes seen in functional ability, BMD, disease activity and HRQoL in the present study.

Lastly, the inclusion of a post intervention assessment allows the sustainability of the present protocol to be examined. If any changes are observed in any of the primary or secondary outcomes of the present study, it is important to be able to report on whether these changes will be sustained after cessation of the intervention, thereby adding strength to the feasibility of the intervention.

